### Participant timeline {13}

Following enrollment, each outcome indicator will be assessed at four time points: before the rTMS intervention (on preoperative day six), after the completion of the rTMS intervention (on preoperative day one), on postoperative day three, and on postoperative day seven. The schedule of enrollment, interventions, and assessments is summarized in the Standard Protocol Items: Recommendations for Interventional Trials (SPIRIT) figure.

### Sample size {14}

Based on previous studies, we assumed a 40% incidence of POCD in elderly patients undergoing knee replacement [5], and following Rodriguez et al. (2005), considered a clinically meaningful absolute reduction of 15 percentage points [18]. With three groups (control, active rTMS, sham) allocated 1:1:1, 80% power, and a two-sided *α* = 0.05, 186 participants are required to detect this difference. Allowing for an anticipated 10% attrition, the planned sample size is 207. This inflation accounts for expected loss to follow-up; if attrition exceeds this allowance and threatens statistical power, the TSC may, on DSMB recommendation and blinded operational data, approve extending recruitment to preserve power without unblinding efficacy.

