**Methods:**

This single-center, randomized, sham-controlled, assessor-blinded, parallel-group trial will enroll 207 elderly patients undergoing TKA and allocate them 1:1:1 to control group, active rTMS group, or sham rTMS group. All participants will receive standardized perioperative management. In addition, patients randomized to the active rTMS group will undergo stimulation of the left dorsolateral prefrontal cortex (DLPFC) at 10 Hz, 2000 pulses per session (5 s trains with 25 s inter-train intervals; 100% resting motor threshold), once daily for five consecutive pre-operative days. The sham rTMS group will follow the identical target and schedule, but the coil will be oriented perpendicular to the skull to avoid effective cortical stimulation. Primary outcome includes incidence of POCD at postoperative day seven (MoCA-based item-level definition). Secondary outcomes include changes in the MoCA total score and a prespecified cognitive subtest battery comprising the Digit Span Test (DST), Digit Symbol Substitution Test (DSST), Trail Making Test (TMT), and Delayed Story Recall (DSR), together with changes in serum inflammatory markers (IL-1β, IL-6, TNF-α, and HMGB1), assessed at preoperative day six, preoperative day one, postoperative day three, and postoperative day seven.

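### The stated 186 participants (62 per arm) give about 43% power, not 80%, to detect the 40% versus 25% difference on which the sample size is based

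*Protocol article*

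**What the plan says.** All the inputs are in the protocol article, Sample size {14}:

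- Incidence: "we assumed a 40% incidence of POCD in elderly patients undergoing knee replacement".
- Effect: the authors "considered a clinically meaningful absolute reduction of 15 percentage points", which puts the active arm at 25%.
- Design and error rates: "With three groups (control, active rTMS, sham) allocated 1:1:1", with "80% power, and a two-sided" alpha of 0.05.
- Result: "186 participants are required to detect this difference".
- Attrition: "Allowing for an anticipated 10% attrition, the planned sample size is 207".

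The Methods paragraph of the Abstract confirms that these are totals over three arms: the trial "will enroll 207 elderly patients undergoing TKA and allocate them 1:1:1 to control group, active rTMS group, or sham rTMS group". So 186 means 62 evaluable patients per arm and 207 means 69 randomised per arm. Trial design {8} sets active stimulation against sham and against standard management, which are pairwise comparisons. Outcomes {12} makes the primary outcome the proportion with cognitive dysfunction on postoperative day seven.

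**The concern.** A fall from 40% to 25% is a moderate difference between two proportions, and 62 per arm is far too few to detect it with 80% power. The section names no test, multiplicity rule or other input that would explain a smaller number.

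If active stimulation truly produces the 15-point benefit, one pairwise comparison will fail to reach significance about 57% of the time (100% − 42.9%). Anyone relying on the 80% claim would give a null result more weight against the treatment than it deserves. Sample size {14} also allows recruitment to be extended to protect power if attrition is high, and the power level that rule refers to is one the trial never had.

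**Working it through.** **Inputs (Sample size {14}).** p1 = 0.40; p2 = 0.40 − 0.15 = 0.25; two-sided alpha 0.05 (z = 1.96); power 80% (z = 0.8416); three equal arms.

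**The plan's own figures.** The attrition step reproduces: 186 / 0.90 = 206.7, rounded up to 207. The 186 itself does not.

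**Required size, pooled-variance formula for two proportions.** The mean proportion is 0.325.

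- n per arm = [1.96 × √(2 × 0.325 × 0.675) + 0.8416 × √(0.40 × 0.60 + 0.25 × 0.75)]² / 0.15²
- = [1.96 × √0.43875 + 0.8416 × √0.4275]² / 0.0225 = 151.9, so 152 per arm
- Three arms: 3 × 152 = 456 evaluable. With 10% attrition: 456 / 0.90 = 506.7, so 507 randomised (169 per arm).
- Stated size relative to need: 186 / 456 = 41%.

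**Power at the stated size.** Power = Φ{[0.15 × √n − 1.96 × √0.43875] / √0.4275}

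- n = 62: Φ[(1.181 − 1.298) / 0.654] = Φ(−0.179) = 42.9%
- n = 69 (no attrition): Φ[(1.246 − 1.298) / 0.654] = Φ(−0.080) = 46.8%
- Exact enumeration at n = 62: 43.0% for the uncorrected chi-square test, 36.0% for Fisher's exact test.

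**Other readings of the same inputs.**

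| Reading | Total needed for 80% power | Power at the stated size |
|---|---|---|
| Pairwise, two-sided 0.05 | 456 (152 per arm) | 42.9% |
| Same, unpooled variance | 450 (150 per arm) | – |
| Same, arcsine | 456 (152 per arm) | – |
| Same, continuity correction | 495 (165 per arm) | – |
| One-sided 0.05 | 360 (120 per arm) | 55.6% |
| Active vs sham and control pooled (62 vs 124) | 348 (116 active) | 52.6% |
| Three-group chi-square, 40/40/25% | 441 | 42.3% |
| Three-group chi-square, 40/25/25% | 405 | 45.4% |
| Three-group chi-square, 40/32.5/25% | 564 | 33.9% |
| Alpha 0.025 for each of two comparisons | 555 (185 per arm) | 32.1% |
| 186 as a two-arm total (93 per arm) | 304 in two arms | 59.0% |

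No reading tried gives a total of 186. Three produce that figure or come close, but none fits the text. Splitting alpha gives 185 per arm, whereas 186 is stated as a total. A change from 40% to 55% with continuity correction gives 186 per arm, but that is an increase, and again a per-arm figure. A fall from 40% to 16% with continuity correction gives 62 per arm, but that is a 24-point reduction.

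**What 62 per arm can detect.** Solving the power formula for p2 at 80% power gives p2 = 0.174, a reduction of 40 − 17.4 = 22.6 points, about one and a half times the target (22.6 / 15 = 1.5).

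**Precision.** The expected 95% half-width for the risk difference is 1.96 × √[(0.24 + 0.1875) / 62] = 0.163, about 16 points. This restates the low power on another scale and is not separate evidence.

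**The case against.** The arithmetic is not open to serious dispute. The best objections concern what follows from it.

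- **Which input is wrong?** The text shows only that 40%, 15 points, 80%, 0.05 and 186 cannot all hold. The effect size or incidence may have been misreported, and the source for the 15 points is not available here. This is fair, and the sponsor would do well to trace the original calculation. But a statement of what 62 per arm can and cannot detect is true whichever figure was at fault.
- **Which comparison?** Active stimulation has two comparators and the section does not say which one is powered. The 43% applies to either one, unadjusted. Splitting alpha would lower it to about 32%, so the caveat makes the finding stronger.
- **Covariate adjustment.** The primary model in Statistical methods {20a} is a covariate-adjusted log-binomial regression, so an unadjusted calculation is approximate. Sample size {14} claims no gain from adjustment, and adjustment could not plausibly do the work of going from 62 to 152 per arm.
- **The article is already cautious.** The Discussion calls the sample modest and urges further scrutiny before the treatment is set aside after a null result; {21b} admits uncertainty about the effect size; a risk ratio with a confidence interval is already planned. This partly reduces the risk of misreading. None of it withdraws the 80% claim or names low power as a reason for a null result.

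This is also not a matter left to an analysis plan. The article gives inputs and a result, and they disagree.

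**Conclusion.** The power statement is wrong as written. For 40% versus 25% at two-sided alpha 0.05, 62 evaluable patients per arm give about 43% power in one pairwise comparison. The stated 80% would need about 456 evaluable patients, not 186. The result assumes the protocol's own incidence and effect, equal arms, one comparison without multiplicity adjustment, and no gain from covariates. Every alternative reading tried leaves power below 60%. Correction is required because this is the stated power for the primary outcome.

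**What to change.** Replace the power statement in Sample size {14} with wording such as:

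> 62 evaluable participants per arm (207 randomised, 10% attrition) give 43% power to detect 40% versus 25% in one pairwise comparison at two-sided alpha 0.05, and 80% power for a reduction of about 22.6 percentage points. A non-significant result will be interpreted from the confidence interval and not as evidence of no effect.

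It would help to name the comparison meant (active versus sham, or active versus control) and, if alpha is to be divided between the two, to give the lower figure of about 32%. If the sponsor finds that an input was misreported, that input should be corrected in the same amendment.

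The cost is protocol and registry wording and a less favourable stated power. The sample size can stay as it is unless the sponsor chooses otherwise, so no extra patients are needed. The article reports enrolment as still under way, so the correction should be made before results are known.

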### Recruitment {15}

Recruitment will take place at Shanghai Fourth People’s Hospital during the elective TKA pathway. Potential participants will be pre-screened at the pre-assessment clinic and on the orthopedic ward against the eligibility criteria (e.g., radiographic severity consistent with Kellgren–Lawrence grade ≥ 3), with written informed consent obtained prior to allocation. Recruitment strategies include surgeon referral at pre-assessment clinics, ward-based screening, and patient-facing materials (posters and flyers). Accrual numbers will be reported only under Trial status; detailed inclusion/exclusion criteria are provided in the “Eligibility criteria {10}” section.

### Patient and public involvement

A Patient Advisory Panel (PAP), comprising two older adults who previously underwent total knee arthroplasty and one caregiver, was consulted during the design phase. Their feedback improved the clarity and accessibility of the participant information sheet and consent form and helped optimize the feasibility and burden of the assessment schedule. During the trial, the PAP will provide consultative input quarterly (start of accrual, mid-study, and prior to database lock), focusing on participant burden, acceptability of procedures, and the preparation of a lay summary of results for dissemination. The PAP has an advisory role only: members will not access identifiable data, will not participate in outcome assessment, statistical analyses, or operational decision-making, and will follow confidentiality requirements. To support meaningful involvement, the study team will provide a brief orientation and plain-language summaries of study procedures and interim progress. Reasonable expenses for attendance will be reimbursed according to institutional policy. PAP contributions will be acknowledged in study outputs; no authorship is conferred by advisory activities.

## Assignment of interventions: allocation

### Sequence generation {16a}

The randomization sequence will be conducted by SAS statistical software version 9.4 (SAS Institute Inc. Cary, NC) by an independent researcher.

### Concealment mechanism {16b}

The researcher responsible for recruitment will assign the eligibility number and then receive a closed, opaque envelope containing the randomization number, allocation, and intervention information.

### Implementation {16c}

The subject assignment will be concealed by placing the assigned tasks in sequentially numbered, opaque sealed envelopes. Clinicians will determine whether subjects are available to participate in the study in strict accordance with the above inclusion and exclusion criteria. The researcher conducting the clinical intervention will open the envelope and be informed of the intervention plan to be delivered to the participant.

## Assignment of interventions: blinding

### Who will be blinded {17a}

Participants, outcome assessors, and statisticians will remain blinded to group allocation. rTMS operators are unblinded due to the nature of the procedure. Blinding success will be evaluated by end-of-treatment allocation-guess questionnaires.

### Procedure for unblinding if needed {17b}

Emergency unblinding is permitted only when knowledge of allocation is essential for clinical management; procedures are held by an independent data manager.

## Data collection and management

### Plans for assessment and collection of outcomes {18a}

All trial personnel will complete role-specific training prior to participant enrollment and will be certified by the PI or delegate. (1) rTMS operators: device operation; coil positioning (F3); motor-threshold determination; stimulation parameters; contraindication screening; and emergency procedures (e.g., syncope/seizure management). (2) Outcome assessors (blinded): standardized administration and scoring of MoCA, DST, DSST, TMT, and DSR with inter-rater checks; maintenance of blinding and separation from intervention delivery. (3) Biospecimen handling staff: venepuncture; processing (centrifugation, aliquoting); − 80 °C storage; ELISA SOPs; chain-of-custody and labeling. (4) AE/SAE monitoring: definitions, reporting timelines, documentation pathways, and escalation to the DSMB per {22}, including immediate reporting and predefined management plans for any adverse reactions.

Training will be documented in logs (date, content/SOP IDs, trainer/trainee signatures), with refresher sessions at least annually or after protocol amendments. Protocol adherence will be monitored through periodic audits and team meetings. During screening and before the first rTMS session, participants will complete a standard rTMS safety questionnaire and undergo physical and neurological examinations to confirm eligibility and safety (see {10}/{11a}).

### Plans to promote participant retention and complete follow-up {18b}

During recruitment, participants will receive comprehensive information on study procedures, requirements, and the importance of completing follow-up. Participants may discontinue rTMS at any time without obligation to provide a reason; withdrawal from the intervention does not constitute withdrawal from follow-up unless consent is revoked. To enhance retention and minimize missing data, we will use multi-modal reminders (phone, text, and written), provide reminders to complete questionnaires at each study visit, offer flexible assessment windows around each time point, and, where feasible, arrange transport assistance. All contact attempts and outcomes will be prospectively logged.

### Data management {19}

Patient data is centrally collected through electronic case report form (eCRF); data is securely protected, and study folders are backed up monthly. Informed consent forms were filed electronically, and paper copies were stored securely. Information on adverse events (AEs) and serious adverse events (SAEs) was entered into 17–34 eCRF for management. All data modifications and analysis steps were documented in detail in eCRF and SPSS, and source data were retained in the electronic medical record. At the end of the study, all data, including patient information, were archived for 30 years to ensure long-term accessibility and compliance.

### Confidentiality {27}

In this study, all participant data will be stored in an anonymized form, which is achieved by assigning a unique study identifier to each participant. The keys to these identifiers will be strictly confined within the research team for the duration of the study and will be properly documented and handled confidentially by the Principal Investigator upon completion of the study based on strict research protocols. It is ensured that no specific information that can identify the patient will be disclosed in the publicly published results.

It is important to note that plans for the collection, laboratory testing, and storage of biological specimens required for genetic and molecular analyses that may be involved in this trial or in the future are not applicable here. Biological samples collected for this study are limited to being used as a basis for safety assessment and are expressly excluded from being used for any form of genetic or molecular research analysis. Further, once the biospecimens have fulfilled their intended use in safety monitoring, they will be immediately and securely destroyed, a move that not only protects the privacy interests of the participants but also strictly adheres to the highest standards of medical ethics.

### Plans for collection, laboratory evaluation and storage of biological specimens for genetic or molecular analysis in this trial/future use {33}

Not applicable because there is no plan for collection, laboratory evaluation, and storage of biological specimens for genetic or molecular analyses that will be used in this trial/in the future.

### Statistical methods

#### Statistical methods for primary and secondary outcomes {20a}

Analyses will follow intention-to-treat. Primary endpoint (POCD at postoperative day seven) will be compared between groups using log-binomial regression to estimate risk ratios (95% CI), adjusted for age, sex, education, and baseline MoCA; logistic regression will be used if convergence issues arise. A supportive analysis will model POCD trajectories at postoperative day three and postoperative day seven using generalized estimating equations with a log link.

Continuous secondary outcomes (MoCA total, DST, DSST, TMT, DSR) will be analyzed using linear mixed-effects models (fixed effects for group, time, and group × time; random intercept for participant), adjusting for baseline. For TMT, if residuals are markedly non-normal, we will report median (IQR) and between-group Hodges–Lehmann differences as pre-specified sensitivity analyses. Inflammatory markers will be log-transformed and analyzed using ANCOVA at each post-op time point with baseline adjustment; results will be back-transformed as geometric mean ratios (95% CI). Missing data will be handled under a missing-at-random assumption via maximum likelihood; multiple imputation (*m* = 20) will be a sensitivity analysis. Multiplicity across secondary outcomes will be controlled by the Benjamini–Hochberg procedure (false discovery rate 5%).

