### Outcomes {12}

#### Primary outcome (five-element specification)

Domain: POCD.

Specific measurement: MoCA administered at four scheduled assessments (preoperative day six, preoperative day one (baseline), postoperative day three, postoperative day seven) by a trained, blinded assessor.

Metric: Binary classification of POCD at each postoperative assessment. POCD is defined a priori as a ≥ 20% decline from baseline in ≥ 2 MoCA items (Newman criteria) [17].

Method of aggregation: The group-level proportion with POCD at postoperative day seven (primary time point); between-group effect expressed as risk ratio with 95% CI from a log-binomial model (logistic regression if non-convergent), adjusted for age, sex, education, and baseline MoCA.

Time point: postoperative day seven (primary); postoperative day three analyzed as supportive.

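### The logistic fallback for the primary model does not say how the planned risk ratio would be obtained, so the primary effect measure may depend on whether the model converges

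*Protocol article*

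**What the plan says.** Two sections of the protocol article fix the primary analysis.

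- Outcomes {12}, Primary outcome: "between-group effect expressed as risk ratio with 95% CI from a log-binomial model (logistic regression if non-convergent", with adjustment for age, sex, education and baseline MoCA.
- Statistical methods {20a}: groups are compared "using log-binomial regression to estimate risk ratios (95% CI), adjusted for age, sex, education, and baseline MoCA", and "logistic regression will be used if convergence issues arise".

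Neither section says that a logistic fit would be converted to risks, and neither names a fallback that estimates a risk ratio directly. The planning values are in Sample size {14}: "we assumed a 40% incidence of POCD in elderly patients undergoing knee replacement", and the authors "considered a clinically meaningful absolute reduction of 15 percentage points".

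**The concern.** A log-binomial model and a logistic model with the same covariates estimate different quantities. The treatment coefficient of the first is a log risk ratio, that of the second a conditional log odds ratio. The two are close when the outcome is rare, but POCD is planned at 25% to 40%. If the logistic model is reported by its usual coefficient, the headline result changes scale according to whether an iterative fit happens to converge. Readers, later meta-analyses and any comparison with the planned 15-point reduction would then work from a number that is not the one the outcome definition promises.

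The fallback could well be used. A log link does not keep fitted risks below 1, and the model combines a common outcome, several covariates and small arms.

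**Working it through.** **Inputs, all from Sample size {14}.** Comparator risk p1 = 0.40. Active risk p2 = 0.40 − 0.15 = 0.25. Before attrition 186 participants in three equal arms, so 186/3 = 62 per arm.

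**The plan's own figures.** The article states no risk ratio or odds ratio to reproduce. The attrition step does reproduce: 186/0.90 = 206.7, rounded up to 207. The 186 itself does not follow from 40% against 25% with 80% power and two-sided 0.05, which needs 152 per arm, or 3 × 152 = 456. That is a separate matter. Here I use 62 only as the planned arm size.

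**Step 1: the two measures at the planning risks.**

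- RR = p2/p1 = 0.25/0.40 = 0.625, a relative reduction of 1 − 0.625 = 37.5%.
- OR = [p2/(1 − p2)]/[p1/(1 − p1)] = (0.25/0.75)/(0.40/0.60) = 0.3333/0.6667 = 0.50, a 50% reduction in odds.
- Link between them: OR = RR × (1 − p1)/(1 − p2) = 0.625 × 0.60/0.75 = 0.50.

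**Step 2: how the gap varies.** With the comparator at 40%:

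| Active risk | RR | OR |
|---|---|---|
| 20% | 0.500 | 0.375 |
| 25% | 0.625 | 0.500 |
| 30% | 0.750 | 0.643 |
| 35% | 0.875 | 0.808 |

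With RR held at 0.625, the OR is 0.60 at 10% comparator incidence, 0.57 at 20%, 0.54 at 30% and 0.50 at 40%. The gap widens with incidence.

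**Step 3: adjusted versions.** These are crude odds ratios, whereas the fallback would give a conditional one. I therefore simulated an adjusted logistic model with assumed log-odds of 0.4, −0.3 and −0.3 per SD for age, education and baseline MoCA, and risks of 0.40 and 0.25 at the covariate means. In large samples the conditional OR was about 0.50, the logistic model standardised to marginal risks gave RR about 0.65, and modified Poisson also gave about 0.65. At 62 per arm the medians were 0.48, 0.65 and 0.65. Both candidate replacements stay on the planned scale and agree with each other.

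**Step 4: how often the fallback might be needed.** The article gives no covariate effects, so this is an assumption with a range. Log-binomial models were simulated at 62 per arm and the planning risks, under slightly different set-ups:

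- no covariate effects: about 5% failures;
- 0.2 log-odds per SD for age, 0.15 for education and MoCA: about 19% to 27%;
- 0.4 for age, 0.3 for education and MoCA: about 57% to 67%. The highest figure also counts any fit with a fitted risk at or above 1 as a failure.

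That is roughly 5% to 60%, and it depends on the fitting algorithm. The section on concomitant care {11d} also puts opioid burden and a psychotropic score into the primary regression models. Their distributions are not given, so I left them out of the range.

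**Step 5: effect on the test.** In simulation at 62 per arm, logistic regression and modified Poisson gave the same significance verdict in 97% to 99% of datasets. Log-binomial and logistic agreed in about 91% to 97% of datasets where log-binomial converged.

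**The case against.** The best defence is that the article never plans an odds ratio. The outcome definition fixes the metric as a risk ratio, and its parenthesis can be read as replacing only the model. A logistic model can deliver a risk ratio by marginal standardisation, and that step could sit in an analysis plan that is not shown. The fallback is also prespecified with a stated trigger, so it is not a choice made after seeing results. All of this is fair, and it limits the point. It does not remove it: the choice of model is already fixed in two sections, the statistical methods section gives no hint of standardisation, and a plain reader would expect the usual logistic output.

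Three stronger readings are tempting, and the document does not support them.

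- A reader might infer that the fallback exaggerates the effect. It does so only if an odds ratio is reported and then read as a risk ratio. A correctly labelled odds ratio is not inflated.
- A reader might infer that non-convergence is to be expected. The covariate effects that decide this are not in the article, and the simulated rate runs from rare to common.
- A reader might infer that the conclusion of the trial is at risk. Both models test the same null hypothesis with the same covariates, and their verdicts nearly always agree.

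**Conclusion.** The point holds as a defect in the definition of the primary effect measure. As written, the fallback does not secure the risk ratio that the article promises, and reported in the usual way it would replace it with a conditional odds ratio. At the planning risks the difference is 0.625 against a crude 0.50. It bears on the size and meaning of the estimate, and hardly on its direction or on the test. The 0.625 and 0.50 rest only on the article's planning risks. The range of about 5% to 60% for non-convergence and the adjusted values rest on assumed covariate effects. The matter is modest and contingent, but it concerns the headline estimate and costs almost nothing to put right.

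**What to change.** In both Outcomes {12} and Statistical methods {20a}, replace the logistic fallback with one that keeps the risk ratio, and name it. Either of these will do:

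- modified Poisson regression (log link, robust variance) with the same covariates; or
- logistic regression with the same covariates, standardised to marginal risks in each arm, reporting their ratio with a delta-method or bootstrap 95% CI.

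Two further steps are optional: making the chosen method the primary model from the start, and stating the same rule for the supportive log-link GEE at days three and seven. Log-binomial is a legitimate primary model, and the article names no logistic fallback for the GEE, so neither step corrects an error.

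The cost is one sentence in each section. Standard software does both methods, and nothing changes in design, sample size or data collection. Enrolment is under way, so the change should be dated and made before unblinding.
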